### Study evaluations

The primary outcome measure was patient mortality 30-days following the stroke. Thirty-day mortality was defined as the proportion of ischemic stroke events that are fatal within 30 days from the onset. Stroke fatality was chosen as main outcome because it is clinically relevant, objectively measured, and reliably coded [5]. The impact of the clinical pathways, comparing the length of the in-hospital stay, the hospital re-admissions rates, the institutionalization rates after hospital discharge, the patients' dependency levels, and complication rates along all the continuum of the care were also analyzed. The list of outcome indicators is reported in table 1.

**Table 1 T1:** The outcome indicators set

**Indicator**	**Measure**	**Criterion met/expected change**	**Source, Year**
In-hospital death rate within 30 days from admission to hospital	(%)	Differences in rates	Clinical Outcome Working Group, 1995, 1997; NHS Centre for Coding and Classification, 1990
In-hospital death rate within 30 days from stroke attack	(%)	Differences in rates	
Post-discharge death rates (1, 3, 6, 12 months after discharge)	(%)	Differences in rates	
In-patients length of stay	Days	Differences in means	Schmidt WP, 2003
Within 9 days length of stay in hospital patients' rate	(%)	Differences in rates	
Pressure ulcers incidence rate	(%)	0%	Clark M, 1991; Effective Health Care, 1995
Overall in-hospital complications rate	(%)	4%	Adams HP Jr, 2003
Overall post-discharge complications rate	(%)	Differences in rates	
Dependency at discharge	FIM scale	Differences in means	Gompertz P, 1993 Wade DT, 1987
Dependency at 6 months after stroke	FIM scale	Differences in means	Hardwood RH, 1994
Institutionalization at discharge	(%)	Differences in rates	Nikolaus T, 2000 Kalra L, 1995
In-hospital re-admission rate (within 30 days from discharge)	(%)	Differences in rates	Ebrahim S, 1987 Milne R, 1990
Return to pre-stroke functioning in daily life rate (with ADL/case mix adjustment)	(%)	Differences in rates	Early Supported Discharge Trialists (Cochrane 2005, Issue 2)

The quality of the care provided to the patients was assessed by monitoring the use of diagnostic and therapeutic procedures during hospital stay and rehabilitation, and by the use of key quality indicators at discharge as reported in previous studies (table 2). The implementation of organized care was also evaluated (table 3).

**Table 2 T2:** The process indicators set

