### Study subjects

The sample included all patients admitted to the hospitals during the experimental period with a principal diagnosis of acute ischemic stroke (ICD-9CM code 434.91) and a minimum age of eighteen. A baseline was verified by comparing the two groups on the admission measuring patients' age, sex, co-morbidities (based on the Charlson-Deyo index), risk factors (including smoking, diabetes, preexisting heart diseases, hyperlipidemia and hypertension) and symptom severity (using the Functional Independence Measure – FIM scale). Patients with hemorrhagic strokes (all ICD-9CM codes included in 431.xx code) and transient ischemic attacks (ICD-9CM code 435.9) were excluded.

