### Data analysis

Data was prospectively collected by local staff for both the interventions and the control groups (physicians and nurses had been trained prior to commencement of the study at two educational events in order to do this). Incentives for the local staff were not used. Data was collected using a standardized data extraction instrument which utilized web technology. This allowed only data without unique personal identifiers, but with a unique study identification code (and therefore anonymous), to be entered into a secure database housed at the University of Eastern Piedmont.

The analysis will be performed by the research team. In addition to common descriptive statistics (Fisher exact and Kruskal Wallis test for categorical and continuous variables, respectively), that will be performed at the cluster level, the differences in the rate of 30-days mortality across groups and according to each variable under study will be evaluated using random-effects logistic regression, thus accounting for the clustering effect [5,22,23]. Variables will be included if significant at the 0.10 level (backward approach), with the exception of age which will be forced to entry. The presence of multicollinearity, interaction and higher power terms will be assessed to check final model validity.

Statistical significance will be defined as a two-sided p-value < 0.05. All analyses will be intention-to-treat and will be carried out using Statistica statistical software.

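### The primary mortality model is built by backward selection at p<0.10 with only age forced, so adjustment for severity depends on the data and neither the arm term nor a baseline-only candidate set is secured

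*Protocol article*

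**What the plan says.** The primary outcome is given under Study evaluations: "The primary outcome measure was patient mortality 30-days following the stroke". Under Data analysis, differences in that rate "across groups and according to each variable under study will be evaluated using random-effects logistic regression". The selection rule follows directly: "Variables will be included if significant at the 0.10 level (backward approach), with the exception of age which will be forced to entry". The section then adds: "The presence of multicollinearity, interaction and higher power terms will be assessed to check final model validity". It sets two-sided significance at 0.05 and declares all analyses intention-to-treat.

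No unadjusted or fixed-covariate primary model is named. Apart from age, no term is said to be kept regardless of its p-value.

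The baseline measures are listed under Study subjects: age, sex, "co-morbidities (based on the Charlson-Deyo index), risk factors" (smoking, diabetes, heart disease, hyperlipidaemia, hypertension) and "symptom severity (using the Functional Independence Measure – FIM scale". They are introduced for comparing the groups at admission.

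The trial also studies variables that arise after randomisation. Quality of care is assessed by "monitoring the use of diagnostic and therapeutic procedures during hospital stay and rehabilitation, and by the use of key quality indicators at discharge" (Table 2), and organised care by the indicators in Table 3.

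**The concern.** A confirmatory comparison needs a model fixed before the data are seen. Here the data choose it, with three consequences of unequal weight.

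- **Baseline adjustment.** Fourteen units were allocated by simple randomisation, so a chance imbalance in case mix between arms is a real risk. FIM and the Charlson-Deyo index are collected and are obvious adjusters, yet each stays only if it passes p<0.10. The arm estimate then depends on which covariates happened to pass, and the reported p-value and interval treat the selected model as if it had been fixed in advance.
- **The arm term.** Age is the sole stated exception to the rule, so the wording does not protect the treatment effect itself.
- **Post-randomisation variables.** The candidates are not limited to baseline. Process and organised-care indicators are what a pathway is meant to change. If they entered the primary model, part of the total effect would be adjusted away, which sits badly with the intention-to-treat statement. Some, such as discharge planning or follow-up within 3 months, are largely available only for survivors.

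**Working it through.** **Inputs.** From Study sample: 238 patients per arm, 8% mortality with the pathway, inflation factor 1.43, 7 clusters per arm, cluster size 24, ICC 0.018. The control rate of 17% is an assumption: the article quotes a range of 8% to 17% and names only the 8% target.

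**Step 1: reproduce the plan's figure.** With pooled variance, n = [z_α·√(2p̄q̄) + z_β·√(p1q1 + p2q2)]² / (p1 − p2)², where p̄ = 0.125. Here √(2p̄q̄) = √0.21875 = 0.4677 and √(0.1411 + 0.0736) = 0.4634.

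- One-sided 5%: (1.645 × 0.4677 + 0.842 × 0.4634)² / 0.0081 = 166; 166 × 1.43 gives 238 per arm, an exact match.
- Two-sided 5%: 211; 211 × 1.43 gives 302, no match.

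The inputs are therefore very probably the plan's own. Sidedness is a separate matter. It is relevant here only because one-sided 5% and two-sided 10% share a critical value, so a retention threshold of 0.10 has about 80% power for the arm.

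**Step 2: chance that the arm would fail p<0.10 if it were a candidate.** Effective n per arm = 238 / design effect. P(removed) = 1 − Φ{[(p1 − p2)·√n − 1.645·√(2p̄q̄)] / √(p1q1 + p2q2)}. Other covariates are ignored.

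| Scenario | Design effect | Effective n | P(arm removed) |
|---|---|---|---|
| 17% vs 8% | 1.43 (stated) | 166.4 | 0.20 |
| 17% vs 8% | 1 + 33 × 0.018 = 1.594 | 149.3 | 0.24 |
| 17% vs 11% | 1.43 | 166.4 | 0.53 |
| No effect | any | any | 0.90 |

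The second row uses 238 / 7 = 34 patients per unit, which differs from the stated cluster size of 24. At 24 the factor is 1 + 23 × 0.018 = 1.414 and the result is 0.19, so the conclusion hardly depends on this input. A simulation with a random-intercept logistic model (7 + 7 units of 34, ICC 0.018, Wald tests) gave 0.20 at 17% against 8% and 0.87 to 0.88 under no effect.

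**Step 3: information available for selection.** Expected deaths = 238 × 0.17 + 238 × 0.08 = 59.5. Nine listed baseline variables plus the arm make ten terms: 59.5 / 10 = about 6 deaths per term, before any process indicator. A fixed model with arm, age, FIM and Charlson-Deyo as single terms has 59.5 / 4 = about 15. If the eight baseline candidates other than age were independent noise, at least one would be kept with probability 1 − 0.9⁸ = 0.57.

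**Step 4: chance that FIM is dropped.** The article gives no prognostic strength for FIM, so a range is assumed. With z = ln(OR per SD) × √[476 × 0.125 × 0.875 × (1 − R²)], R² with the other covariates from 0 to 0.3, and clustering ignored, P(dropped) = 1 − Φ(z − 1.645):

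- OR 1.3: 40% to 52%
- OR 1.5: 10% to 21%
- OR 2.0: below 1%

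**The case against.** The best defence is that Data analysis names the comparison across groups separately from the variables under study, so the selection sentence most naturally refers to covariates. The arm contrast is the trial's main hypothesis, and the authors probably meant to keep it. This stands in part: deletion of the arm is one reading of the text, not what it says. The removal probabilities are also little more than one minus power at 0.10. An arm term with p above 0.10 is already non-significant at 0.05 in that model, so the loss is the estimate and interval, not the verdict.

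A reader might also infer that the Table 2 and Table 3 indicators are in the candidate set. The article does not say so. It calls them indicators of care quality and organisation, and the interest in their effects on outcomes belongs to the second and third objectives, which may have their own models. What stands is that nothing excludes them: "according to each variable under study will be evaluated using random-effects logistic regression" carries no restriction to baseline.

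A third tempting inference is that severity will be left out. Step 4 does not support it: a strongly prognostic FIM would almost always survive.

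Finally, an article may leave a covariate list to the analysis plan. That does not answer the point, because the selection rule itself is stated here, and an analysis plan that follows it inherits the fault.

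**Conclusion.** The point holds as a should-fix. The only model described for the primary outcome is chosen by a p-value rule with age as the sole forced term. Adjustment for severity and comorbidity is therefore data-dependent, with about 60 expected deaths and 14 simply randomised units, and the final inference ignores the selection. How far this distorts the arm's p-value cannot be computed from the article.

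Two gaps in the wording add to this: the arm is not explicitly retained, and candidates are not confined to baseline. On the literal reading the arm term would be lost in about 20% to 24% of trials at 17% against 8%, and in about 90% under no effect, where an estimate with its interval is most needed. These figures rest on the assumed 17% control rate, the stated ICC, and a normal approximation without covariates. The article does not establish that the arm will be dropped, that mediators will enter, or that FIM is likely to be lost.

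**What to change.** For the primary analysis, replace backward selection with a fixed random-effects logistic model that always contains the arm, age and a short pre-specified set of baseline covariates already collected (for example admission FIM and the Charlson-Deyo index), with unit as random effect. State that no variable measured after randomisation enters this model, and that the arm estimate and its interval are reported whatever the p-value. The exact covariate list is open to choice, but it should be settled before outcome data are examined.

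Keep selection procedures, interaction and higher-order terms, and models with process or organised-care indicators as exploratory secondary analyses.

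The cost is a change of wording. The sample size of 476 is unaffected by this change, and no new data are needed.

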### Ethics

The project received ethical clearance as a prerequisite of approval for funding from the Italian Ministry of Health, according to the Italian Ministry of Health law number (ex art. 12bis D.lgs 229/99). The managers in each unit have consented to their clinic taking part in the trial. Patient's consent to be randomized to the intervention or control arms has not been obtained, because according to the study design randomized occurred at the unit level. However all individual patients gave consent to participate in the study and had the opportunity to withdraw from the study at any time. All patients' data was managed according to the Italian Data Protection act.

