**Figure 1 F1:**
[figure not shown]
Flow diagram of the progress of the units through the trial.

Nine units were excluded because they did not meet the inclusion criteria and five units withdrew after the project commenced following a decision by their management (three units withdrew after project pre-test and two units withdrew after project kick off). One unit could not provide reassurance that they would not implement a pathway if assigned to the control group and therefore they were not included in the study sample. The remaining units were randomized to either of the two arms. A simple randomization was carried out before the intervention and patient recruitment started, using a computer-generated sequence with allocation concealment. Fourteen units were selected and randomized. Blinding of patients and clinicians was not possible.

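### The sample is defined both as all stroke admissions and as consenting patients, so 30-day mortality may be biased if losses at consent differ by arm

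*Protocol article*

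**What the plan says.** - **Who is in the sample.** Study subjects: "The sample included all patients admitted to the hospitals during the experimental period with a principal diagnosis of acute ischemic stroke", aged eighteen or over. No consent condition appears there.
- **Consent.** Ethics: "Patient's consent to be randomized to the intervention or control arms has not been obtained", since allocation was at unit level. The next sentence reads: "However all individual patients gave consent to participate in the study and had the opportunity to withdraw from the study at any time".
- **Order of events and blinding.** Randomization (text after Figure 1): "A simple randomization was carried out before the intervention and patient recruitment started", and "Blinding of patients and clinicians was not possible".
- **Primary outcome.** Study evaluations: "Thirty-day mortality was defined as the proportion of ischemic stroke events that are fatal within 30 days from the onset". Deaths in the first days after onset therefore count as events.
- **Data and analysis.** Data analysis: "Data was prospectively collected by local staff for both the interventions and the control groups". The main comparison is a random-effects logistic regression, by intention to treat. Covariates are chosen by backward selection at the 0.10 level, and only age is forced in.

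**The concern.** The two descriptions of the sample agree only if every eligible patient was asked and agreed, in person or through someone else, and none withdrew. That is unlikely in acute stroke, where the article itself expects 8% to 17% to die within 30 days. Some patients may die before anyone can ask them, some will lack capacity, and some may refuse. A consent step is thus likely to be related to severity and early death, which is the primary outcome.

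In a cluster trial this matters more than in an individually randomized one, because patients enter after their unit's arm is known and the staff are unblinded. Randomizing units balances the admissions, not the patients who get through a later filter. Intention-to-treat keeps enrolled patients in their arm but cannot bring back those never enrolled. The baseline comparison likewise sees enrolled patients only, and admission FIM, the severity measure, may drop out of the model.

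**Working it through.** **The plan's own figures.** The article gives no consent, refusal or withdrawal rate, so there is no figure on this point to reproduce. The mortality inputs come from the Study sample section: 17% (upper end of its range, read as the control rate) and 8% under the pathway. These reproduce the stated 238 per arm with a one-sided 5% test: 166 × 1.43 = 237.4, rounded up to 238. With the two-sided test of the Data analysis section the result is 211 × 1.43 = 301.7, or 302. That mismatch is a separate matter. It is used here only to explain why power starts at about 70%: it is two-sided, at an effective size of 238 / 1.43 = 166.4 per arm.

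**Formula.** Let p be the true 30-day mortality, and cD and cS the shares of deaths and of survivors that are enrolled.

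- Observed rate = p·cD / (p·cD + (1 − p)·cS)
- Observed odds = true odds × cD/cS

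The marginal odds ratio is therefore distorted only when cD/cS differs between the arms. All values of cD and cS below are assumptions.

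**Equal loss of deaths, all survivors enrolled, true rates 17% and 8%**

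| Deaths lost in each arm | Observed rates | Difference (points) | Odds ratio | Two-sided power |
|---|---|---|---|---|
| 0% | 17.0% vs 8.0% | 9.0 | 2.355 | 70% |
| 10% | 15.6% vs 7.3% | 8.3 | 2.355 | 66% |
| 30% | 12.5% vs 5.7% | 6.8 | 2.355 | 58% |
| 50% | 9.3% vs 4.2% | 5.1 | 2.355 | 46% |

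Power assumes that recruitment still reaches 238 per arm.

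**Unequal loss, no true effect (17% in both arms)**

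- 90% against 70% of deaths enrolled, all survivors enrolled: 0.153 / (0.153 + 0.83) = 15.6% against 0.119 / (0.119 + 0.83) = 12.5%. The false difference is 3.0 points and the false odds ratio 0.9 / 0.7 = 1.29. If the pathway arm is the one at 70%, the chance of a significant result in its favour is about 12%, against a nominal 2.5%.
- The same, but with 95% against 85% of survivors enrolled: 0.153 / (0.153 + 0.7885) = 16.3% against 0.119 / (0.119 + 0.7055) = 14.4%. The false difference falls to 1.8 points and the odds ratio to (0.90/0.95) / (0.70/0.85) = 1.15. The gap narrows because the arm losing more deaths also loses more survivors.
- Deaths lost in the pathway arm only, all survivors enrolled: a loss of 10%, 30% or 50% gives a false difference of 1.4, 4.5 or 7.7 points. The chance of a significant result favouring the pathway is 5%, 21% or 55%.

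**Unequal loss that hides an effect.** With true rates of 17% and 8%, losing 30% of deaths in the control arm only gives 12.5% against 8.0%: 4.5 points instead of 9.

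**The case against.** The strongest reply is that nothing in the article reports a loss. It does not say when consent was taken or that anyone was left out for incapacity or early death, and it does not rule out consent by a representative. A journal article may leave such procedures to the full protocol. The two sections can also be read together as clinical eligibility plus a condition for taking part. This stands as far as it goes: a reader might infer that early deaths were in fact lost and that the comparison is biased, and the article supports neither. It does not remove the ambiguity, because consent by a representative would not recover refusals, withdrawals or deaths before anyone was asked.

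A reader might also infer that pathway units would recruit severe patients differently because they had a facilitator. The Intervention section gives that person the task of helping implementation, including staff education, and mentions no part in consent. Data collection is described alike in both arms: trained local staff, no incentives, one standardized instrument. Different loss by arm is possible because entry was unblinded and came after allocation, but the article shows no specific cause.

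A third tempting reading is that any loss of deaths weakens the planned comparison. Equal loss does not change the marginal odds ratio, and the planned model works on that scale. What falls is the absolute rates, the risk difference and the power.

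Lastly, there are partial safeguards. The arms are compared at baseline on age, sex, comorbidity, risk factors and admission FIM, so a gross imbalance in severity could show, and these variables can enter the model. They do not guarantee correction.

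**Conclusion.** The point holds as a risk of bias, not as shown bias. The article gives two different sample definitions for a mortality outcome, and the second applies a filter after unblinded allocation that is plausibly related to early death. The effect estimate is distorted if the enrolled share of deaths, relative to survivors, differs by arm. With no true effect at 17%, the assumed 90% against 70% gives a false difference of 3.0 points with all survivors enrolled, and 1.8 points when survivors are lost in the same pattern. Over the wider range shown, the false difference runs from 1.4 to 7.7 points.

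The direction is unknown. The sizes rest on assumed capture rates, on reading 17% as the control rate, and on marginal rather than random-effects calculations. The documents cannot say whether the true difference in loss is large, small or nil, which is why the counts below are needed.

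**What to change.** 1. Reconcile Study subjects with Ethics. Define the 30-day mortality denominator as all eligible admissions per unit, and state how patients who die early, lack capacity, refuse or withdraw are counted.
2. Have every unit report anonymous counts, by arm: eligible admissions in the period, patients not consented or withdrawn, and in-hospital deaths within 30 days among them. Eligibility rests on a diagnosis code and age, so unit records should suffice.
3. Add a mortality analysis by arm on consented plus non-consented patients, shown beside the consented-only analysis. To compare like with like, use in-hospital death within 30 days in both; Table 1 already lists such indicators.
4. Keep admission FIM in the patient-level model together with age, whatever backward selection gives.
5. Use fuller data on non-consented patients, under a waiver, proxy or deferred consent, only if ethics permits. The documents do not show whether it would.

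The cost is a short screening count per unit. Two limits remain: 30-day status after discharge will be incomplete for non-consented patients, and counts alone carry no FIM, so the analysis that includes those patients cannot be adjusted for severity.

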## Discussion

The aim of this study is to improve the quality of care through clinical pathways and thus should not imply any risk for the patients affected by the study. It is difficult to imagine that interventions based on better evidence and appropriate use of technologies and drugs could worsen the quality of care when compared to usual care. However despite continuing international interest in implementing clinical pathways, the evidence base for their effectiveness in improving the quality of stroke care is still inconclusive [8].

Clinical pathways could be defined as a complex intervention in which a number of separate elements are essential to the functioning of the intervention, but the "active ingredient" that is effective is difficult to specify [11]. For this reason it could be problematic to evaluate properly clinical pathways mainly because of the difficulty of keeping the intervention replicable and recognizable. However we think that a cluster randomized controlled trial design is the most appropriate to evaluate clinical pathways [24]. To standardize the intervention we defined as standard the steps in the change process or the key functions that the elements of the intervention were meant to improve according to each context. Moreover our indicators were driven by the theory and concerned the functions provided by the key elements of the clinical pathways that were based on expected adherence to the same evidences. So we think that this helped to keep the integrity of the intervention in each site [10,25].

We also think that the outcome measures chosen were well-suited to measuring the impact clinical pathways have on stroke care, because they were measures that evaluated most of the perspectives of stroke care from acute to rehabilitation settings. In particular two outcome measures – mortality and organized care – can help to investigate the new hypothesis which is to understand how clinical pathways can work. In fact the management of patients affected by stroke involves the expertise of several professionals, which can result in poor coordination or inefficiencies in patient treatment, and clinical pathways can significantly improve the outcomes of these patients. However, the active ingredient of clinical pathways is unclear, so we think that our study will help to better understand which mechanisms within the clinical pathways can really improve the quality of care.

